**Discussion:**

The NKF-NUS intervention builds upon previous research emphasizing the importance of empowering patients in taking control of their treatment management. The trial design addresses weaknesses of previous research by use of an adequate sample size to detect clinically significant changes in biochemical markers, recruitment of a sufficiently large representative sample, a theory based intervention and careful assessment of both clinical and psychological endpoints at various follow up points. Inclusion of multiple dependent variables allows us to assess the broader impact on the intervention including both hard end points as well as patient reported outcomes. This program, if found to be effective, has the potential to be implemented within the existing renal services delivery model in Singapore, particularly as this is being delivered by health care professionals already working with hemodialysis patients in these settings who are specifically trained in facilitating self management in renal patients.

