### Sample calculation

Using serum phosphate levels as a physiological index of adherence to diet and medication) and Kidney disease specific QoL as primary outcomes, a total sample size of 126 and 128 respectively, were calculated. This was using 80% power (alpha = 0.05) to detect a significant absolute change of 1.5% in phosphate control and of 5 points (0.5 standard deviation) in the physical and mental component subscale scores in kidney disease QoL short form questionnaire [40]. Taking the larger number of 128 participants (64 in intervention and 64 in control group), a final total number of 154 participants (77 in each group) is needed to ensure at least an 80% final response rate is met (attrition/drop-out rate estimated at 20%). A target sample of 154 participants will be sought.

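### The phosphate sample size of 126 does not follow from a 1.5% absolute change on either usual reading, so the stated detectable phosphate effect is wrong as written

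*Protocol article*

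**What the plan says.** The Sample calculation section of the protocol article sizes the trial on two outcomes, serum phosphate and kidney-disease quality of life (QoL), and reports "a total sample size of 126 and 128 respectively, were calculated". Power is 80% and alpha 0.05 for both.

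- **Phosphate.** The variable is introduced as a level: "Using serum phosphate levels as a physiological index of adherence to diet and medication". The target is then worded "to detect a significant absolute change of 1.5% in phosphate control". No mean, SD or control rate is printed for phosphate, and the article does not say whether phosphate control means a proportion of patients or a concentration.
- **QoL.** The target is a change "of 5 points (0.5 standard deviation) in the physical and mental component subscale scores".

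The larger figure is carried forward ("Taking the larger number of 128 participants (64 in intervention and 64 in control group") and raised to 154 for 20% attrition.

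The Discussion part of the Abstract and the main Discussion both present as a strength the "use of an adequate sample size to detect clinically significant changes in biochemical markers". Of the biochemical markers listed under Primary outcome measures, phosphate is the only one with a sample size calculation.

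**The concern.** A 1.5% absolute change is a very small effect on the scales on which phosphate is normally analysed, and 126 is a small trial. The two do not sit together without some explanation, and the number 126 is what a moderate effect of half a standard deviation would give.

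At stake is what the trial can claim about phosphate. If the printed target is wrong or on the wrong scale, the claim of adequate power for biochemical change rests on an effect far smaller than the design can detect. A reader of a null phosphate result could take it as evidence against effects that the trial had little chance of seeing.

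**Working it through.** **Inputs.** From the Sample calculation section: 80% power, alpha 0.05, equal arms, 126 in total for phosphate (63 per arm), 128 for QoL (64 per arm), phosphate target 1.5%, QoL target 0.5 SD. Two-sided testing is assumed because sidedness is not stated; one-sided testing at 0.5 SD would give 50 per arm, which matches neither figure. Base rates and coefficients of variation (CV) below are assumptions, shown as ranges. Write k = (1.960 + 0.842)² = 7.849.

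**1. The QoL figure reproduces.** A two-sample t-test at 0.5 SD needs 63.77, so 64 per arm and 128 in total.

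**2. What 126 corresponds to.** The normal approximation at 0.5 SD is n = 2k/0.5² = 62.8, so 63 per arm and 126 in total. In reverse, 63 per arm implies a standardised difference of √(2k/63) = 0.499.

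**3. Reading A: difference in the proportion controlled.** n per arm = k[p(1−p) + (p+0.015)(1−p−0.015)]/0.015².

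| Base rate p | n per arm |
|---|---|
| close to 0%, or 98.5% | 515 |
| 5% | 3,777 |
| 10% | 6,690 |
| 30% | 14,853 |
| 50% | 17,434 |
| 70% | 14,434 |
| 90% | 5,853 |

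No base rate comes near 63. One-sided testing lowers the floor only to about 410. Solving the same formula for the difference with n = 63 gives 23.9 points at 30%, 23.5 at 50% and 19.5 at 70%. At these base rates, the power of 63 per arm to show a 1.5-point increase is about 4%.

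**4. Reading B: 1.5% of mean phosphate.** n per arm = 2k(CV/0.015)².

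| Assumed CV | n per arm | Power at 63 per arm |
|---|---|---|
| 3% | 63 | 80% |
| 10% | 698 | 13% |
| 20% | 2,791 | 7% |
| 30% | 6,280 | 6% |

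Only an SD of 3% of the mean returns 126.

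**5. Is an SD of 3% of the mean plausible on the article's own figures?** The article gives no mean. The Background gives a level of 5.5 to 6.0 mg/dL above which mortality risk rises considerably, and expresses risk per 1 mg/dL. If 5.5 mg/dL is used purely as an illustrative mean, 3% of it is 0.165 mg/dL. The 0.5 mg/dL threshold band would then span 0.5/0.165 = 3.0 SD, and a 1 mg/dL step 1/0.165 = 6.1 SD. That is hard to square with a population in which the Background describes differences of that order as clinically meaningful and reports wide variation in adherence. On the same illustration, a 1.5% change is 0.0825 mg/dL.

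**The case against.** The strongest reply is that the article sizes on phosphate levels and omits the SD. With a difference of 1.5 and an SD of 3.0 in the same unit, the formula gives 63 per arm exactly, and 1.5 is then itself 0.5 SD. This stands as arithmetic, so a reader who infers that 126 cannot possibly have come from 1.5 goes further than the article allows. It does not rescue the printed sentence: if the unit is percent of the mean, the required SD is implausibly small, and if it is some other unit, the sentence names the wrong one.

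Four further points have force.

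- A reader might infer that 126 simply is the 0.5 SD calculation. The article ties 0.5 SD only to QoL, and the match needs a normal approximation for phosphate beside a t-test for QoL. It is the simplest explanation, not a documented one.
- A reader might infer that thousands per arm are needed whatever the scale. That depends on the base rate or CV: at extreme base rates, or at a CV of 10%, the need is in the hundreds.
- The Statistical Considerations section plans ANCOVA with the baseline value as covariate, which reduces the required size by the factor 1 − r². At a CV of 20% the 2,791 becomes 2,094 with r = 0.5, 1,424 with r = 0.7 and 531 with r = 0.9. None is near 63.
- An article may leave the source of an SD to the full protocol, so its absence alone is not the defect. The defect is a target effect that, as worded, does not fit the number beside it.

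Finally, QoL sets the final number, so nothing about recruitment changes. That is correct and limits the consequence to the power claim.

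**Conclusion.** The point holds as a wrong or mis-scaled target effect behind a stated power. On the proportion reading, 126 is unreachable at any base rate: the need is at least about 515 per arm, and 14,400 to 17,400 at 30% to 70%. On the percent-of-mean reading it is reached only with an SD of 3% of the mean, against about 700 to 6,300 per arm for assumed CVs of 10% to 30%.

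If patients are treated as independent, 63 per arm detects about 0.5 SD of serum phosphate with 80% power. The article describes allocation by dialysis shift within centres, so once clustering is allowed for, the detectable difference is larger than that.

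The results assume two-sided testing and no baseline adjustment; the baseline-adjusted figures under the objection do not alter the conclusion. The 128 and the 154 derived from it do not depend on the phosphate target. The adequacy statements in the Abstract and Discussion do not themselves cite 1.5%, but phosphate is the only biochemical calculation available to support them.

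**What to change.** 1. Retrieve the inputs of the phosphate calculation and establish the scale and unit of the 1.5 figure. Do not print 0.5 SD simply because it matches 126.
2. Replace the 1.5% wording with the difference in serum phosphate, in concentration units, that the planned sample detects with 80% power. Give the SD and its source; the dialysis centres' routine records are an obvious one.
3. Calculate that difference allowing for clustering by dialysis shift, with the assumed intracluster correlation and cluster size stated. About 0.5 SD is the value for independent patients and should be labelled as such if shown.
4. Limit the adequacy claims in the Abstract and the main Discussion to that difference, and to phosphate unless the other markers are also sized.

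The cost is a check of the original calculation, an SD look-up and some rewording. The downside is that the stated detectable effect becomes less favourable. No extra patients are needed for this correction.

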**Methods/Design:**

This is a multicentre parallel arm block randomized controlled trial (RCT) of a four session group self management intervention for hemodialysis patients delivered by health care professionals compared to standard care. A total of 176 consenting adults maintained on hemodialysis for a minimum of 6 months will be randomized to receive the self management intervention or standard care. Primary outcomes are biochemical markers of clinical status and adherence. Secondary outcomes include general health related quality of life, disease-specific quality of life, mood, self efficacy and self-reported adherence. Outcomes will be measured at baseline, immediately post-intervention and at 3 and 9 months post-intervention by an independent assessor and analysed on intention to treat principles with linear mixed-effects models across all time points. A qualitative component will examine which aspects of program participants found particularly useful and any barriers to change.

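### The recruitment target is given as both 154 and 176 without reconciliation, and 154 leaves about 123 evaluable patients, not the 128 required, at the plan's own 20% drop-out

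*Protocol article*

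**What the plan says.** The Sample calculation section names serum phosphate and kidney-disease-specific quality of life as the outcomes used for sizing, with totals of 126 and 128 respectively at 80% power and alpha 0.05. The quality-of-life calculation targets a difference "of 5 points (0.5 standard deviation) in the physical and mental component subscale scores". The larger total, 128 (64 per arm), is carried forward. Drop-out is put at 20%, and the section concludes that "a final total number of 154 participants (77 in each group) is needed to ensure at least an 80% final response rate is met". It closes with "A target sample of 154 participants will be sought".

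The Methods/Design paragraph of the abstract gives another number: "A total of 176 consenting adults maintained on hemodialysis for a minimum of 6 months will be randomized". The figure 176 appears nowhere else in the article and has no derivation.

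**The concern.** There are two separate defects.

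**Conflicting targets.** Both 154 and 176 are current text, and each is stated as the trial's size. They differ by 22 patients, which is 22/154 = 14% of the smaller figure. A reader cannot tell when recruitment is complete, or against which number a shortfall should be judged.

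**Attrition arithmetic.** An allowance for a drop-out proportion d should divide the evaluable number by (1 − d). Multiplying by (1 + d) always gives too few patients, because the loss applies to everyone randomised and not only to the evaluable number. The figure 154 matches the multiplication, so the trial would miss its own evaluable number if drop-out ran exactly as assumed. There is no margin to absorb this, because 128 is the minimum for 80% power in the plan's calculation.

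**Working it through.** **Inputs, all from the Sample calculation section unless noted**

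- Power 80%, alpha 0.05. Sidedness is not stated. Two-sided is inferred because a one-sided calculation gives 50 per arm, which does not match 64.
- Difference 5 points = 0.5 SD, so the implied SD is 10.
- Evaluable total 128, allocated 64 and 64.
- Drop-out 20%.
- Stated total 154 (77 per arm); abstract total 176.

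**Step 1: reproduce 128.** By the normal approximation, n per arm = 2(1.960 + 0.842)²/0.5² = 62.8, so 63. The t-test version gives 63.8, so 64 per arm and 128 in total. This matches the plan. The 126 for phosphate cannot be recomputed, because "detect a significant absolute change of 1.5% in phosphate control" comes with no SD or control value.

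**Step 2: reproduce 154.**

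- Multiplying: 128 × 1.2 = 153.6, rounded up to 154; per arm 64 × 1.2 = 76.8, rounded up to 77. Both match the plan exactly.
- Dividing: 128/0.8 = 160; per arm 64/0.8 = 80. This does not match, and rounding cannot explain a gap of 6.
- Starting from 126 does not give 154 either: 126 × 1.2 = 151.2, so 152, and 126/0.8 = 157.5, so 158.

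**Step 3: what each total leaves at 20% loss, and the power for 0.5 SD.** The comparison is unadjusted and individually randomised. The normal approximation is Φ(0.5 × √(n/2) − 1.96), with n evaluable per arm.

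| Randomised | Evaluable | Per arm | Power, t-test | Power, normal |
|---|---|---|---|---|
| 154 | 154 × 0.8 = 123.2 | 61.6 | 78.6% | 79.2% |
| 160 | 160 × 0.8 = 128.0 | 64.0 | 80.1% | 80.7% |
| 176 | 176 × 0.8 = 140.8 | 70.4 | 83.8% | 84.3% |

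**Step 4: the loss each total can bear while keeping 128.** For 154: 1 − 128/154 = 16.9%. For 176: 1 − 128/176 = 27.3%.

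So 154 is about 5 evaluable patients short under the plan's own assumption, and 176 is about 13 above (140.8 − 128 = 12.8).

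**The case against.** The strongest reply is that the shortfall is slight and may vanish in the planned analysis. The gap is 0.8 to 1.4 percentage points of power and 6 patients randomised. The Statistical Considerations section plans ANCOVA with baseline as a covariate, which multiplies the residual variance by about 1 − r², where r is the baseline-to-follow-up correlation. If the 0.5 SD refers to raw scores, offsetting the loss needs 1 − r² = 123.2/128 = 0.9625, that is r of about 0.19. The article gives no r, so this is an assumption, but it is a low bar. This stands as a limit on the consequence. It does not make 154 the right inflation of 128, and the sample-size text takes no credit for adjustment.

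The power figure also belongs to one outcome. Quality of life is called primary in the Sample calculation section but is listed as secondary in the abstract, in the Study Objectives and among the measures. Against the phosphate requirement of 126, 154 falls short by about 3 evaluable patients (126 − 123.2 = 2.8), and the power there cannot be computed. This too stands.

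Two stronger readings are tempting, and the article supports neither:

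- A reader might take the two numbers together as showing that the trial is underpowered. Only 154 falls below 80%; on the same inputs 176 exceeds it.
- A reader might notice that 160 × 1.1 = 176 and infer a 10% allowance for randomisation by dialysis shift. The article mentions no design effect, intracluster correlation or cluster size, so this is numerical coincidence until the sponsor says otherwise.

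The absence of any clustering allowance in the sample-size text is a separate matter and adds no weight to this point.

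**Conclusion.** Both defects are real. The article states two incompatible recruitment targets, 154 and 176, and gives no basis for the second. This is the more consequential half, because it leaves the size of the trial undefined by 22 patients. Separately, 154 is wrong on the plan's own inputs: the consistent total is 160, and 154 yields about 123 evaluable where 128 are required.

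The power consequence of the second defect is minor, at about 79% instead of 80%. That figure rests on a two-sided 5% test, a 0.5 SD difference in the quality-of-life component scores, exactly 20% loss in each arm, no baseline adjustment and no clustering. Adjustment would raise it and any positive intracluster correlation would lower it; the article quantifies neither. If 176 is the operative target, the attrition slip does no harm to power under the stated inputs, and what remains is an unexplained number and an incorrect calculation in the text.

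**What to change.** State one target in both the abstract and the Sample calculation section, and correct the attrition step to 128/0.8 = 160 (80 per arm).

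- If 154 stands as the target, say that 20% loss leaves about 123 evaluable and about 79% power for 0.5 SD, before clustering and baseline adjustment.
- If 176 is the operative target, replace 154 in the Sample calculation section and give the actual source of 176. Do not describe it as including a design-effect allowance unless one was in fact made; if it was, state the intracluster correlation and cluster size used.

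The cost is wording: a slightly less favourable stated power if 154 is kept, or 6 more patients than 154 if 160 is adopted. Adopting 176 asks for nothing beyond what the abstract already commits to.

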### Measures

The following demographic information will be collected before the start of the trial: age, gender, ethnicity, education, religious affiliation, marital and employment status, perceived work ability and household income, length of time since diagnosis, prescribed drugs currently taken, and co-morbid medical conditions.

#### Primary outcome measures

Beginning at baseline (Time 1) and continuing into follow up (Time 2, Time 3, Time 4) regular chart reviews will be conducted to abstract clinical, laboratory, and pharmacological data including:

(1) Interdialytic weight gain: The amount of weight gained between the end of one dialysis session and the beginning of the next. This is a validated marker of adherence to fluid restriction/regulation.

(2) Blood pressure

(3) Serum phosphate and calcium × phosphate product indicating a patient's adherence to prescribed oral phosphate binder medications and dietary phosphate restriction.

(4) Serum potassium indicating adherence to dietary recommendations.

#### Other Clinical Measures

(1) Medical notes will be also reviewed to record other serological data (urea, creatinine, hemoglobin, intact parathyroid hormone and albumin as well as urea reduction ratio and Kt/V), all prescribed medication and relevant information regarding dialysis history and dialysis related events (e.g. access complications) during the study period.

(2) Attendance for dialysis (skipping and shortening behaviours) and Health services utilization (number of admissions, emergency room visits) will also be monitored.

(3) The End Stage Renal Disease Severity Index (ESRD-SI) [41] will provide a measure of co-morbid illnesses and other complications of ESRD.

(4) The Charlson Comorbid Index (CCI) will be used to consolidate comorbidity burden. CCI scores will be computed pursuant to the methods described by Beddhu et al. [42].

#### Secondary process and outcome measures

The potential benefits of the intervention are quite broad, so multiple secondary outcomes are of interest and will therefore be measured with the following self report questionnaires. License agreements have been obtained for all measures. When no standardized translations of the instruments are available, translation validity will be confirmed using forward-backward method.

(1) QoL as assessed using the Kidney Disease QoL Short Form - KDQoL-SF [43]. This measure contains the Short form 36 health survey questionnaire (SF-36) supplemented with scales targeted at particular concerns of individuals with kidney disease: symptoms, effects of kidney disease on daily life, burden of kidney disease, cognitive function, work status, sexual function, quality of social interaction and sleep. To minimize burden of completion the SF 36 of the scale has been replaced with the SF12, a shortened validated version of SF36 to gather information on eight health concepts: physical functioning, role limitations due to physical and emotional health, mental health, bodily pain, general health, vitality and social functioning. These items are then scored using a norm-based method providing a component summary scale score for both mental and physical Health Related Quality of Life [44]. The instrument has been proved reliable and valid in dialysis patient populations in Singapore [45].

(2) Generic/Global quality of life was assessed using the *World Health Organization Quality of Life *questionnaire (WHOQOL-BREF) [46]. It is a self-report inventory of generic QoL consisting of 26 original items. The items fall into four domains: a) *Physical Health*, b) *Psychological Health*, c) *Social Relationships *and d) *Environment*, while two items provide a measurement of an *Overall QoL/Health *facet. The scale has demonstrated good psychometric properties. It is rated on a 5-point Likert scale and the range of scores is between 1-20 with higher scores indicating better quality of life.

(3) Anxiety and depression according to the Hospital Anxiety and Depression Scale (HADS) [47]. This is a widely used, self-administered questionnaire specifically developed to detect anxiety and depression states in hospital and medical out-patient clinic settings with good reliability and responsiveness [48]. It is composed of two 7-item scales, one for anxiety and one for depression. The original English version has been translated into and validated in many languages, including Chinese [49,50].

(4) Self-efficacy will be assessed using 2 measures: one is specific to dialysis patients and the self efficacy for managing chronic disease scale [51]. The latter comprised the sum of self-efficacy for managing the general demands of chronic disease. Respondents rated their confidence for performing various chronic disease self-management tasks including, seeking information about their conditions, obtaining help from others and communicating with physicians, maintaining role function, and managing symptoms.

The dialysis specific Self-Efficacy Scale [27] was devised specifically for the purposes of this study. Respondents are asked to indicate their level of confidence in managing dialysis specific demands related to diet, fluid intake and medication using eight items scored on 10 point likert rating scale ranging from 'not all confident' to 'totally confident' in line with the Self efficacy for managing chronic disease scale [51]. An expert panel of renal health professionals has reviewed the items and the scale was successfully piloted with a small group of hemodialysis patients (N = 4).

(5) The Health Education Impact Questionnaire (HEIQ™) is a reliable measure with high construct validity, designed to evaluate outcomes from patient education and self-management interventions for people with chronic conditions. It comprises eight domains to assess more proximal program outcomes [52]; Health directed behaviour, Positive and active engagement in life, Emotional well-being, Self monitoring and insight, Constructive attitudes and approaches, Skill and technique acquisition, Social integration and support, Health service navigation.

(6) The Renal Adherence Attitudes Questionnaire (RAAQ) [53] - The RAAQ is a 26-item scale measuring general attitudes toward compliance. The scale is composed of Likert-type statements, which measure a patient's attitudes toward social restrictions, well being, self-care/support and acceptance.

(7) The Renal Adherence Behaviour Questionnaire (RABQ) [53]- The RABQ comprises 25 items measuring self-reported dietary and fluid intake compliance. Specific dimensions; include compliance to fluid restrictions; compliance regarding potassium and phosphate restrictions, compliance regarding self-care; compliance regarding sodium intake; and compliance in times of particular difficulty.

(8) Beliefs about medication [54]. The measure comprises two 5-item sub-scales assessing beliefs about the necessity of prescribed medication ('necessity' sub-scale) and concerns about prescribed medication based on beliefs about the danger of dependence and long-term toxicity and the disruptive effects of medication ('concerns' sub-scale).

(9) The Medication Adherence Report Scale (MARS). The five-item MARS asks respondents to rate the frequency with which they engage in non adherent behaviors (e.g., deciding to miss a dose, forgetting to take a dose). Scores for each of the five items are summed to give a total score ranging from 5 to 25 where higher scores indicate higher levels of self-reported adherence [55].

(10) Six items developed for the study will be included to measure frequency of non adherent behaviours to dietary recommendations (3 items) and fluid intake (3 items) (e.g. forgetting, adjusting).

(11) Qualitative assessment

The trial also includes a qualitative sub-study. The qualitative research involves in-depth interviews of intervention participants at 3 and 9 months after delivery of the NKF-NUS self management course. The aim of this work is to explore participants' attitudes towards the program, their satisfaction with content, delivery and duration and their progress with regards to self management.

Participants will be asked to describe whether they have tried making any changes in their fluid intake, diet and general lifestyle or thinking as a result of the intervention; whether these changes have been made successfully or unsuccessfully and the reasons why. Participants will also be asked to highlight the strengths and weaknesses of the intervention and to give feedback on the program in five open-ended questions.

A short intervention evaluation questionnaire developed for the purposes of the study will also be administered at the 3 and 9 month follow up to rate patients' satisfaction with the content, length, delivery of individual sessions, dynamics and interaction with the facilitators and with other patients in the group.

